#### Trial medication

Trial medication bottles are distributed to the trial site pharmacy in batches. On dispensing, the adhesive label indicating treatment allocation is removed by the pharmacist and placed in the participant’s pharmacy file. Trial medication is provided to the trial researcher who delivers the medication to the participant at assessment 0. Medication bottles are replaced at 3-week intervals. Participants are provided with feedback on their medication adherence at each assessment using eCAP™ technology (Med-ic eCAP™, Information Mediary Corp, see Adherence for details). The number of capsules remaining in each medication bottle is audited on return.

#### Safety monitoring

AEs are recorded by trial research staff at each assessment and reviewed by the trial physician. Face-to-face medical assessments are scheduled for all severe and serious adverse events (SAEs), and also at the discretion of the trial physician or at the request of the participant. Any ongoing AEs at the end of the trial are followed for at least 7 days, and ongoing SAEs for at least 30 days, with all AEs followed until stabilisation or resolution. All participants are entitled to compensation in accordance with the Medicines Australia Compensation Guidelines.

#### Discontinuation of medication and withdrawal from the trial

Participants are free to discontinue the trial medication or withdraw from the study at any time. Investigators may discontinue trial medication or withdraw a participant from the trial for the following reasons: pregnancy, no longer meeting the inclusion criteria, failing to take the medication for 7 or more days, significant non-compliance with the study protocol, disease progression that requires discontinuation of the trial medication or a clinical condition for which it would not be in the best interest of the participant to continue taking the trial medication. Follow-up assessments are completed regardless of medication discontinuation for all participants who remain consented into the study.

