### Setting and study population

Participants are being recruited via outpatient settings in Melbourne (Turning Point and Eastern Health), Geelong (Barwon Health) and Wollongong (Illawarra Drug and Alcohol Service) in Australia. All participants are volunteers. They provide written informed consent prior to participation (see Additional file 2 for the participant information sheet and consent form). Inclusion criteria are that participants must be aged 18–60 years, meet DSM-IV criteria for methamphetamine dependence, be seeking to reduce their methamphetamine use but are not currently undergoing substance use treatment (including pharmacotherapy for substance use disorders), are not in need of acute care for psychiatric or other medical conditions, do not have a primary psychotic disorder, are able and willing to comply with the trial protocol, and have no contraindications for NAC. Contraindications for receiving the trial medication include: previous hypersensitivity to NAC; use of medications containing NAC or thought to be hazardous if taken with NAC (e.g. carbamazepine and nitroglycerin); a known or suspected active systemic medical disorder including cancer or other medical condition that may exacerbate the risk of AEs from NAC (recent gastrointestinal ulcers or renal stones, epilepsy or history of seizures, asthma or atopy); and, surgery within the past 28 days. Further, participants must not be pregnant (confirmed at the eligibility assessment), lactating or planning to fall pregnant during the trial.

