#### Recruitment and screening

Participants are recruited through advertisements (e.g., Facebook, media activity, and flyers in needle and syringe programs) and word of mouth. They are screened by phone. Potentially eligible participants are consented by trial staff and then undergo a face-to-face eligibility assessment (1.5 to 2 h in total) to confirm their eligibility and to obtain information on demographics, drug use and psychiatric history. All participants undergo a medical assessment to confirm further their eligibility prior to randomisation. Randomisation must occur within 28 days of eligibility being confirmed. Eligible participants are provided with a list of local health service providers and are free to access drug treatment and other health services during the trial. Ineligible participants are offered referral to local alcohol and other drug services.

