#### Assessments

The eligibility assessment and assessment 0 are conducted at the trial site clinic. Weekly assessments (assessments 1–12) are scheduled thereafter (with a leeway of −2 days to +4 days). These may be done at a public venue convenient to the participant (e.g., a café or shopping mall) to enhance retention. They take around 40 min each. Detailed contact information is collected on all participants and text message reminders are sent prior to appointments to enhance follow-up rates. Saliva samples are taken at each of the follow-up assessments using a Quantisal Oral Fluid Collection Device™. Participants undergo a final medical assessment within 30 days of completing the trial or on discontinuation of their medication. All participants are provided with referral information for alcohol and other drug treatment services at the close of the study.

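### One list of grounds covers both stopping medication and withdrawal from the trial, so investigators may end participation for a week without medication, non-compliance or lapsed eligibility, with follow-up not expressly protected

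*Protocol article*

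**What the plan says.** The section 'Discontinuation of medication and withdrawal from the trial' opens by naming two separate acts open to participants: "Participants are free to discontinue the trial medication or withdraw from the study at any time". It then gives investigators the same two options under a single list: "Investigators may discontinue trial medication or withdraw a participant from the trial for the following reasons: pregnancy, no longer meeting the inclusion criteria". The list continues: "failing to take the medication for 7 or more days, significant non-compliance with the study protocol". Its last two grounds concern clinical reasons for not staying on the drug. The section closes: "Follow-up assessments are completed regardless of medication discontinuation for all participants who remain consented into the study".

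Among the inclusion criteria in 'Setting and study population' are states that can change after entry. Participants must "be seeking to reduce their methamphetamine use but are not currently undergoing substance use treatment", and must be people who "are not in need of acute care for psychiatric or other medical conditions". Under 'Recruitment and screening', however, eligible participants are "free to access drug treatment and other health services during the trial". The Discussion plans to record such treatment, compare the arms on it and adjust where they differ.

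The primary measures are the percentage of days of use in the 28 days before assessments 4, 8 and 12, and saliva tests at assessments 1 to 12 ('Primary endpoint'). Their analysis is by intention to treat, with unobserved days censored ('Analysis of primary outcomes') and missing data multiply imputed by chained equations ('Analysis of secondary outcomes').

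**The concern.** Stopping a drug and stopping data collection have different consequences. Stopping the drug is a clinical decision that an intention-to-treat analysis accommodates, provided outcomes are still collected. Ending participation removes those outcomes. Here the two share one list, and three of its grounds could plausibly track the outcome. A participant who stops taking capsules for a week, no longer wants to cut down, or needs acute psychiatric care may well be using methamphetamine differently from one who does not.

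Outcomes removed on such grounds would be missing for reasons related to methamphetamine use, and the loss would be avoidable, because the participant need not have withdrawn consent. A medication lapse is also easy to see: under 'Trial medication', electronic adherence data are fed back at every weekly assessment.

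**Working it through.** **1. What the wording allows.** The opening sentence, the section heading and the 'or' in the investigator sentence all treat medication discontinuation and trial withdrawal as distinct. The grounds are not divided between them. The closing sentence sets two conditions: it applies regardless of medication discontinuation, and to people who remain consented. It does not mention a person whom an investigator has withdrawn from the trial and who has not revoked consent. No other section of the article settles that case.

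**2. What would be lost per person.** Inputs: weekly assessments 1 to 12; three 28-day windows (days 1–28, 29–56, 57–84); one saliva test per assessment. Assume the nominal schedule, ignoring the visit leeway, with the last data taken at assessment k. Then:

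- days observed = 7k
- saliva tests forgone = 12 − k

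| Withdrawn at | Days observed | Window 1 | Window 2 | Window 3 | Saliva tests forgone |
|---|---|---|---|---|---|
| k = 2 | 14 | 14/28 | 0/28 | 0/28 | 10 |
| k = 6 | 42 | 28/28 | 14/28 | 0/28 | 6 |
| k = 9 | 63 | 28/28 | 28/28 | 7/28 | 3 |

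Assessment 2 is the earliest point for a seven-day lapse that follows a dosed first week. A seven-day lapse is 7/84 = 8.3% of the course. These figures hold for anyone who leaves at those visits for any reason. They give the cost of each use of the power, not its total effect.

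**3. What the analysis recovers.** Because the endpoint is a percentage and unobserved days are censored, a part-filled window (14/28 or 7/28) may still contribute. An empty window and an uncollected saliva test can only be imputed. Standard chained-equations imputation relies on the missingness being explained by observed data. That is doubtful if the withdrawal reflects a change in use occurring around or after the last visit. The mitigation is therefore partial.

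**4. Attrition allowance.** 'Sample size estimation' allows 20% attrition: 0.20 × 90 = 18 per arm, leaving 72. The article gives no expected number of investigator-led withdrawals, so neither their share of the 18 nor any bias can be calculated.

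**The case against.** The best answer is the closing sentence itself. Its stated limit is consent, and an investigator's decision about a medication lapse does not revoke consent, so a withdrawn participant might still be followed. Several grounds (pregnancy and the two clinical ones) are naturally reasons to stop the drug, and a week's lapse most naturally leads there too. The rest of the article favours retention: outreach visits ("These may be done at a public venue convenient to the participant"), adjustment for concomitant treatment, and an aim in the Discussion to study sub-optimal dosing, which needs outcomes from poor adherers. The power is also discretionary, and a journal article condenses a fuller protocol.

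Most of this stands as a limit on the point. The consent reading is possible but not stated, and it would leave the separate power to withdraw from the trial with little meaning. The retention aims show intent, and they argue for correcting the rule. The point rests on a power and grounds that the article states, not on detail it leaves out.

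A reader might infer more than the documents support:

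- **That follow-up definitely ends, or that there is none after medication is stopped.** The closing sentence expressly keeps follow-up after medication is stopped, and can be read to go further.
- **That participants who enter treatment will be removed.** Read literally, they no longer meet an inclusion criterion. But access to treatment is expressly allowed and adjustment for it is planned, so this is awkward wording, not a conflict of intent.
- **That the clause contradicts intention-to-treat.** That principle governs how randomised people are analysed; permitting withdrawals does not contradict it.
- **That investigators could select by arm.** 'Randomisation and blinding' keeps trial staff and investigators blind to allocation.

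**Conclusion.** The point holds as a weakness in a stated rule. Investigators have a discretionary power to end trial participation on grounds that are plausibly related to methamphetamine use, and continued outcome collection for those participants is not expressly secured. If the power is used and follow-up stops, the loss per person runs from 3 saliva tests and most of one window (withdrawal at assessment 9) to 10 tests and two empty windows (withdrawal at assessment 2).

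This rests on three assumptions: that the power is exercised, that withdrawal from the trial ends data collection, and that the triggering events relate to use. The documents establish none of these as fact, so the size and direction of any bias are undetermined. The change is worth making because the loss is avoidable and prevention is inexpensive. Nothing here shows that the trial's result would be biased.

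**What to change.** - Make the listed reasons grounds for stopping study medication only.
- State that the inclusion criteria apply at entry, and that neither non-adherence nor starting substance use treatment is a ground for ending follow-up.
- Continue timeline followback and saliva collection to assessment 12 unless the participant withdraws consent or contact would be unsafe for the participant or staff.
- Report any investigator-led trial withdrawals by arm, with reasons.

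The cost is a minor amendment through the ethics committees that approved version 3.0, a reminder to the three sites, and staff time for visits already scheduled at about 40 minutes each. Per participant retained, that is at most 10 × 40 = 400 min (6.7 h) from assessment 2, 6 × 40 = 240 min (4.0 h) from assessment 6, or 3 × 40 = 120 min (2.0 h) from assessment 9. Counting from the 77 of 180 randomised by 9 May 2019, the change would reach up to 180 − 77 = 103 participants still to enter, plus those still in follow-up.

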### Endpoints and assessments

Measures and measurement time points are presented in Table 1.

**Table 1 Tab1:** Measures taken at each assessment

	Eligibility Assessment	Weekly trial assessments												
		0	1	2	3	4	5	6	7	8	9	10	11	12
Demographics, drug use history, CIDI (methamphetamine dependence), MINI (depression, psychotic disorders and mania), DIP (family history of psychotic disorders), RCQ, BCIS, BIS items, SAPAS	x													
Saliva samples			x	x	x	x	x	x	x	x	x	x	x	x
TLFB for days of methamphetamine use	x	x	x	x	x	x	x	x	x	x	x	x	x	x
Days of other substance use	x	x	x	x	x	x	x	x	x	x	x	x	x	x
Adverse events			x	x	x	x	x	x	x	x	x	x	x	x
Concomitant medications		x	x	x	x	x	x	x	x	x	x	x	x	x
Concomitant treatment		x	x	x	x	x	x	x	x	x	x	x	x	x
SDS		x	x	x	x	x	x	x	x	x	x	x	x	x
CEQ		x	x	x	x	x	x	x	x	x	x	x	x	x
AWQ		x	x	x	x	x	x	x	x	x	x	x	x	x
BPRS items		x	x	x	x	x	x	x	x	x	x	x	x	x
WPAI-GH		x	x	x	x	x	x	x	x	x	x	x	x	x
EQ-5D-5L		x	x	x	x	x	x	x	x	x	x	x	x	x
Health service use and criminal justice involvement		x	x	x	x	x	x	x	x	x	x	x	x	x
TSQM						x				x				x

*CIDI* Composite International Diagnostic Interview, *MINI* Mini International Neuropsychiatric Interview, *DIP* Diagnostic Interview for Psychosis, *RCQ* Readiness to Change Questionnaire, *BCIS* Beck Cognitive Insight Scale, *BIS* Birchwood Insight Scale, *SAPAS* Standardised Assessment of Personality – Abbreviated Scale, *TLFB* timeline followback, *SDS* Severity of Dependence Scale, *CEQ* Craving Experience Questionnaire, *AWQ* Amphetamine Withdrawal Questionnaire, *BPRS* Brief Psychiatric Rating Scale, *WPAI-GH* Work Productivity and Activity Impairment Questionnaire – General Health V2, *EQ-5D-5L* Five-dimension five-level version of EuroQol questionnaire, *TSQM* Treatment Satisfaction Questionnaire – Medication

#### Primary endpoint

The primary outcome is methamphetamine use. There are two measures of this endpoint:Days of methamphetamine use during the 12-week active medication phase, assessed using the timeline followback method (TLFB) [31] and updated weekly. The outcome measure is the percentage of days on which methamphetamine is used during the 28 days prior to assessments 4, 8 and 12. The TLFB has 88% sensitivity, 96% specificity and 0.77 test–retest agreement for the use of amphetamines in the past 30 days [31].The number of methamphetamine-positive saliva samples taken at assessments 1–12. Saliva is collected with an Alere Quantisal Oral Fluid Collection Device™ and the presence of methamphetamine confirmed using mass spectrometry with a detection cut-off of >25 mg/L.

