**Methods/design:**

This is a two-arm parallel double-blind placebo-controlled three-site randomised trial (ratio 1:1) using permuted block randomisation, with variable block sizes. It is stratified by site, sex and whether the methamphetamine is injected or not. Participants (*N* = 180; 60 per site) need to be dependent on methamphetamine, interested in reducing their methamphetamine use and not currently receiving treatment for substance use disorders. The trial is being conducted in outpatient settings in Melbourne, Geelong and Wollongong, Australia. Participants will receive either 2400 mg oral NAC or a matched placebo, delivered as a take-home medication for 12 weeks. Two 600 mg capsules are self-administered in the morning and two more in the evening. Adherence is being monitored using eCAP™ medication bottle lids, which record the date and time of each occasion the bottle is opened. The primary outcome is methamphetamine use during the 12-week trial medication period, measured as (a) days of use, assessed using the timeline followback, and (b) methamphetamine-positive saliva tests, taken weekly. Secondary measures include weekly assessment of methamphetamine craving, severity of methamphetamine dependence, methamphetamine withdrawal symptoms and psychiatric symptoms (depression, suicidality, psychotic symptoms and hostility). Adverse events are monitored at each weekly assessment. Tolerability is assessed using the Treatment Satisfaction Questionnaire for Medication.

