### Statistical considerations

#### Sample size estimation

The sample size of 90 participants per treatment arm is designed to detect a mean between-group difference of 3.5 days versus 6.0 days of methamphetamine use per month during the 12-week trial medication period with at least 80% power at *p* < 0.025 (0.05 / 2 to accommodate two primary outcome measures) and with 20% attrition (i.e., a final sample of at least 72 participants per treatment arm). The expected effect size is based on data from the Methamphetamine Treatment Evaluation Study (MATES) [42]. Participants who did not receive treatment in that cohort showed a reduction in methamphetamine use from a mean (standard deviation) of 12.8 (7.4) days per month at baseline to 6.0 (6.7) days per month at the 12-weekfollow-up. Our estimate of a minimal clinically meaningful reduction in use is based on outcomes for outpatient counselling derived from MATES: 11.2 (8.8) days per month to 3.5 (6.9) days per month at 12 weeks. Our estimate of 20% attrition is based on our previous research [42, 50, 51]. No interim analyses are planned. Statistical power was estimated using the SAMPSI command in Stata (Version 14.2, StataCorp LLC, College Station, Texas).

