#### Efficacy analysis

All tests will be two-sided with significance set at *p* < .025 for each of the two primary endpoints and *p* < .01 for each of the secondary endpoints. Significance for all other tests will be set at *p* < .05. The analyses will be conducted blind to condition.

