##### Analysis of primary outcomes

Intention-to-treat analyses will be conducted for the primary outcomes. The effect of the trial medication on days of methamphetamine use (percentage of days used in the past 28 days) will be tested using a baseline (assessment 0) vs. medication phase (three repeats: assessments 4, 8 and 12) by treatment condition (NAC vs. placebo). Unobserved days (e.g., due to hospitalisation or incarceration) will be censored. The effect of NAC on methamphetamine-positive saliva will be tested using a main effect for treatment condition (NAC vs. placebo) on saliva test results (positive vs. negative) from assessments 1–12 (12 repeats).

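### The saliva cut-off that defines the second primary measure is printed as >25 mg/L, an implausibly high limit for detecting the drug; the unit needs confirming and correcting

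*Protocol article*

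**What the plan says.** The protocol article has two primary measures of methamphetamine use. The second is described under Primary endpoint as "The number of methamphetamine-positive saliva samples taken at assessments 1–12". The same section names the specimen and device ("Saliva is collected with an Alere Quantisal Oral Fluid Collection Device™") and gives the rule for a positive result: "presence of methamphetamine confirmed using mass spectrometry with a detection cut-off of >25 mg/L". The abstract mentions weekly saliva tests but gives no limit.

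Under Analysis of primary outcomes, each sample enters the model as positive or negative, with 12 repeats per participant and a main effect of treatment. Under Efficacy analysis, "All tests will be two-sided with significance set at *p* < .025 for each of the two primary endpoints". The cut-off is therefore the rule that produces the data for one of the two primary tests.

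**The concern.** The section presents the figure as a limit for establishing that the drug is present. A detection limit should sit well below the concentrations expected after use. At 25 mg/L it appears to sit above most of them.

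Two outcomes are possible, and both need action:

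- **The printed value is applied.** Many samples from participants who had used the drug would be called negative. The measure would lose much of its ability to separate the arms, and with it the trial's biological check on self-reported days of use.
- **The laboratory applies another value.** The trial itself may be sound, but the published definition of a primary endpoint is then not the one used, and a reader could not reproduce it.

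**Working it through.** **1. Unit conversion.** 25 mg/L × 1,000,000 ng/mg ÷ 1,000 mL/L = 25,000 ng/mL = 25,000 µg/L. The article does not derive the cut-off, so there is no calculation of the sponsor's to reproduce.

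**2. Mass-balance check.** The formula is: saliva concentration = (A ÷ V) × r. Here A is the amount of drug in the body when the sample is taken, V the distribution volume and r the saliva-to-plasma ratio. The article gives none of these, so all are assumed and varied: A from 50 to 1,000 mg; V = 42, 140 or 280 L; r = 1, 2, 5 or 10. That gives 12 combinations of V and r for each amount.

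| A (mg) | Lowest (V = 280, r = 1) | Highest (V = 42, r = 10) | Combinations above 25 mg/L |
|---|---|---|---|
| 50 | 0.18 mg/L | 11.9 mg/L | 0 of 12 |
| 100 | 0.36 mg/L | 23.8 mg/L | 0 of 12 |
| 250 | 0.89 mg/L | 59.5 mg/L | 2 of 12 (V = 42, r ≥ 5) |
| 500 | 1.79 mg/L | 119 mg/L | 3 of 12 |
| 1,000 | 3.57 mg/L | 238 mg/L | 6 of 12 |

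A worked entry: 100 ÷ 140 × 2 = 1.43 mg/L, and 25 ÷ 1.43 = 17.5, so this case lies about 17 times below the limit.

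**3. Amount needed to reach the limit.** Rearranged, A = 25 × V ÷ r, for r from 10 down to 1:

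- V = 42 L: 105 to 1,050 mg
- V = 140 L: 350 to 3,500 mg
- V = 280 L: 700 to 7,000 mg

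**4. Timing.** A is what remains at sampling, not what was taken. The Sample size estimation section expects 3.5 to 6.0 days of use per month. Over 28 days that is 3.5 ÷ 28 = 12.5% to 6.0 ÷ 28 = 21.4% of days. With one sample a week, many would fall a day or more after last use, when A has already declined.

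**5. What lost positives would cost (illustration only).** Assume true positive rates of 60% and 40%, one test per participant, the planned 72 per arm after attrition and two-sided alpha 0.025 (z = 2.241). If a fraction s of true positives is detected, the rates become 0.6s and 0.4s. Power = Φ[(0.2s − 2.241 × SE₀) ÷ SE₁], with SE₀ pooled and SE₁ unpooled.

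For s = 1: SE₀ = √(2 × 0.25 ÷ 72) = 0.0833 and SE₁ = √(0.48 ÷ 72) = 0.0816. Power = Φ[(0.2 − 0.1868) ÷ 0.0816] = Φ(0.16) = 56%.

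| Share of true positives detected | Power |
|---|---|
| 100% | 56% |
| 50% | 19% |
| 10% | 4.5% |
| 1% | 1.9% |

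The planned 12 repeats would give different absolute values, and the normal approximation is poor in the last row. The table shows the direction and steepness of the loss; it does not predict this trial's power.

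**The case against.** The strongest reply is that nothing in the article conflicts with the figure. No second cut-off is given, and the case rests on pharmacology that the article does not supply. **That stands.** A reader might infer an internal contradiction or an arithmetic error, but the document supports only implausibility under stated assumptions.

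A reader might also infer that nearly every sample in both arms would be negative. **The documents do not support that either.** No positive rate can be computed from them. With 100 mg the most favourable combination reaches 23.8 mg/L, only just under the limit; 105 mg would reach it, and larger amounts exceed it in some combinations. Drug residue in the mouth soon after smoking could also push isolated samples over. A single calculation, such as 100 mg in 40 L giving 2.5 mg/L, makes the gap look like a clean factor of ten only because it sets the saliva-to-plasma ratio to 1.

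A third reply is that this is a slip in a condensed article, or a micro sign lost in typesetting or file conversion, and that no one will dichotomise at 25 mg/L. **This is quite likely, but it explains the error and does not remove the need for correction.** The article states the threshold outright, so it is not a detail left to the analysis plan. It does mean that one should not conclude that the assay was run at this level. Sample size (based on days of use), significance levels and model are unaffected if the figure is only a misprint.

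Finally, one might assume that the full protocol, analysis plan or registry entry repeats the figure. Those were not available, so no error in them is claimed.

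**Conclusion.** The point holds as a probable unit error in the operative definition of a primary measure. The printed limit of 25,000 ng/mL is not credible as a threshold for the presence of the drug: with 50 or 100 mg in the body, no combination examined reaches it. Exceeding it takes a larger amount together with a small distribution volume or a high saliva-to-plasma ratio. Under these assumptions, and with weekly sampling, literal use would miss most true use and sharply reduce the endpoint's ability to show an effect.

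If micrograms per litre was meant, the intended limit is 25 ng/mL, 1,000 times lower. That reading is an inference for the sponsor to confirm. The volumes, ratios, amounts and positive rates used here are all assumptions.

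**What to change.** Confirm the cut-off and its unit against the laboratory's written method. Correct the figure in the endpoint definition, and in any other trial document found to repeat it. Apply that single value to the samples from all 12 assessments, and settle it before unblinding.

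The cost is one query to the laboratory and one corrected figure. The Trial status section reports 77 of 180 participants randomised by 9 May 2019, so there was room to do this without touching the design, the sample size or the analysis model.
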